#### Measures

##### Primary outcomes

The primary outcomes include medication utilization and medication adherence. We define medication utilization (or uptake) as at least one pharmacy fill of a medication in the drug class of interest during each one-year time window (two pre- and two post-intervention); this is analogous to the calculation of many performance measures, including several Healthcare Effectiveness Data and Information Set (HEDIS) measures [37]. For statins and ACE/ARBs, medication uptake rates will be explored in the subset of individuals identified by claims or laboratory data to have a clear clinical indication for use (*e.g*., statins for individuals with diagnosed hyperlipidemia or LDL cholesterol above guideline recommended levels [5]).

We define medication adherence using medication possession ratios (MPRs). The MPR is the ratio of the cumulative days of medication supply obtained, divided by the number of days supply which would be needed for perfect adherence. To calculate the MPR, each day in a quarter will be evaluated as 'covered' or 'not covered' by a refill; if all days are 'covered' by a refill then the MPR will be 100%. MPRs will be calculated separately for each medication class (listed in Table 1) for each quarter. Rules for handling early refills, dosage increases, and within-class drug switches will be applied and have previously been described [38]. For hospitalizations, we assume medications are hospital-supplied until discharge, at which time the home supply is resumed. While the MPR is a measure of refill adherence rather than a direct measure of medication taking behavior, it has been shown to correlate well with patient outcomes [39].

**Table 1 T1:** Drug classes receiving co-payment reductions: focus on diabetes trial

**Glycemic Agents**
Metformin
Sulfonylureas
Thiazolidinediones
All other glycemic agents (except insulin*)
**Antihypertensive Agents**
ACE-Inhibitors & Angiotensin Receptor Blockers (ACE/ARB)
Beta blockers
Calcium Channel Blockers
Diuretics
Other antihypertensives
**Lipid-Lowering Agents**
HMG-CoA Reductase Inhibitors (statins)
Zetia
Other lipid lowering agents
**Antidepressants**
SSRSs/SNRIs
Tricyclic agents
Other antidepressants

*At the time of the intervention, M-CARE already waived copayments for Insulin.

##### Secondary outcomes

Secondary outcomes include health care utilization rates (*e.g*., counts of outpatient visits, ER visits, hospitalizations) and health care spending. Pharmaceutical and non-pharmaceutical expenditures will be examined both overall and disaggregated into the costs borne by the payer and those assumed by the patient (*i.e*., out-of-pocket costs).

##### Model covariates

To ensure findings are due to the co-payment reductions and not to underlying differences between the two groups, models will adjust for age, gender, comorbidity, member status (employee, spouse or dependent), and number of medications taken. Comorbidity is assessed using the Deyo modification to the Charlson comorbidity index [40], a well-validated measure of the burden of comorbid illness that was developed specifically for use with claims data.

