### Hypotheses

We hypothesized that the removal of financial barriers to evidence-based, high-value therapies will result in improved uptake and adherence, and a more efficient use of resources. Specific hypotheses are:

1. Compared to individuals with diabetes with usual co-pays, those receiving targeted co-payment reductions for high-value therapies will increase uptake of these therapies and improve adherence to these therapies (conditional upon their use).

2. Compared to payers for individuals with diabetes with usual co-pays, payers for those receiving value-based co-payment reductions will incur higher pharmaceutical spending, lower non-pharmaceutical cost growth, and lower overall cost growth. Importantly, we do not hypothesize an absolute financial savings over previous years. Rather, we posit that the rate of non-pharmaceutical cost growth will be slower in the intervention group than in the controls.

3. Among individuals with diabetes and depression, compared to individuals with usual co-pays, individuals receiving value-based co-payment reductions for high-value therapies will have improved uptake and adherence to antidepressants and improved uptake and adherence to other study medications (statins, ACE/ARBs, other antihypertensives and glycemic agents).

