### Study design

The study employs an interrupted time series design, with medication adherence rates assessed at three-month intervals (unit of observation is the patient-quarter), beginning 30 months prior to the intervention (the 'pre' period) and continuing through the duration of the 30-month intervention (the 'post' period). This study design provides a strong test of the intervention's impact on medication adherence, separate from other ongoing temporal changes in adherence [34]. The advantage of this 'difference-in-difference' design is that any change in the control group values may reflect naturally occurring changes over time (perhaps due to policy or medical care changes), while any change in the UM intervention group values will reflect both the same naturally occurring trends, as well as the impact of the value-based co-payment reductions.

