##### Statistical power

The intervention can increase appropriate medication use in two ways: by increasing use in those currently not on the medications of interest (*i.e*., increasing uptake), and by increasing the adherence of patients who are taking the medications. Based upon our original estimated sample sizes of 2,131 in the intervention group and 4,000 in the control group, and an average initial uptake rate of 50% (based upon statins and ACE/ARBs), we will have 80% power to detect an effect of 3.8% change in medication utilization at a p = 0.05 significance level. In turn, based upon average pre-intervention medication adherence rates of 65% (based on statins and ACE/ARBs), we will have 80% power to detect an effect of 3.5% change in MPR (*i.e*., adherence) at the p = 0.05 significance level.

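### The medication count used for adjustment is not fixed before the intervention; if it is updated afterwards, it contains the uptake outcome and biases that effect towards zero

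*Protocol article*

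**What the plan says.** The section Model covariates states that "models will adjust for age, gender, comorbidity, member status (employee, spouse or dependent), and number of medications taken". The reason given is "To ensure findings are due to the co-payment reductions and not to underlying differences between the two groups". No measurement window is attached to the medication count, and the class under analysis is not excluded from it. The sentence refers to the models in general, and Health care expenditures reuses the regression approach described for adherence.

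Three other places bear on this:
- Hypotheses and Statistical power make new use an intended effect. One of the two routes to more appropriate use is "by increasing use in those currently not on the medications of interest".
- Primary outcomes defines uptake as "at least one pharmacy fill of a medication in the drug class of interest during each one-year time window".
- Table 1 lists 15 rows of drugs with reduced co-payments: 4 glycemic, 5 antihypertensive, 3 lipid-lowering and 3 antidepressant.

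**The concern.** Of the listed covariates, the medication count is the one that the intervention is meant to change. A patient who starts a statin because it has become cheaper scores on the uptake outcome and also adds one to any count taken in the same window. Adjusting for that count compares patients at an equal number of drugs, which holds constant part of what the co-payment reduction does.

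At stake is a primary outcome. A real rise in uptake could be reported as small or absent. Hypothesis 2 expects higher pharmaceutical spending, and starting more drugs is one route to it, so that analysis would be partly affected too. For MPR, which is conditional on use, the link is less direct and no size is claimed here.

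**Working it through.** **1. The plan's own figure.** Statistical power gives "original estimated sample sizes of 2,131 in the intervention group and 4,000 in the control group", 50% initial uptake, a 3.8-point change and 80% power at 0.05 (two-sided assumed). For two proportions:

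- pooled p = (2,131 × 0.538 + 4,000 × 0.50) / 6,131 = 0.5132
- SE under no effect = √[0.5132 × 0.4868 × (1/2,131 + 1/4,000)] = 0.01340
- SE under the effect = √[0.538 × 0.462/2,131 + 0.25/4,000] = 0.01338
- z = (0.038 − 1.96 × 0.01340) / 0.01338 ≈ 0.88, so power ≈ 0.81

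The adherence figure (65% to 68.5%, MPR treated as a proportion) gives 0.79. Both agree with the stated 80%, and neither depends on the covariate.

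**2. Count fixed before the intervention.** In a linear difference-in-difference model on a fixed panel, a value that is the same before and after for each patient cannot alter the group-by-period term. In simulations with a true effect of 3.8 points, the estimates without a count and with a pre-intervention count were identical to two decimals in every mixed-drug scenario (3.74 to 3.88).

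**3. Count from the same window.** Suppose K classes are counted, with similar use and similar mutual correlation, and m of them, including the one analysed, each rise by δ. The count then rises by mδ. By symmetry, the slope of one class on the total is 1/K. The adjusted effect is therefore

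δ − (1/K) × mδ = δ × (1 − m/K).

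The documents do not give K, m or the correlations, so the values below are assumptions. The simulations used latent correlations of 0, 0.1 and 0.3.

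| Classes counted (K) | Responding (m) | Formula, points | Simulated, points |
|---|---|---|---|
| 12 | 1 | 3.8 × 11/12 = 3.48 | 3.43 to 3.53 |
| 8 | 1 | 3.8 × 7/8 = 3.33 | 3.35 |
| 12 (4 targeted, 8 other) | 4 | 3.8 × 8/12 = 2.53 | 2.52 to 2.53 |
| 8 (4 targeted, 4 other) | 4 | 3.8 × 4/8 = 1.90 | 1.89 to 2.00 |
| 12 (8 targeted, 4 other) | 8 | 3.8 × 4/12 = 1.27 | 1.23 to 1.33 |
| targeted only (4, 8 or 14) | all | 0 | −0.19 to 0.07 |

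The loss is m/K: 8% to 13% if one class responds, 33% to 67% if several do, and all of it in the extreme case. A separate simulation with the actual group sizes (2,507 and 8,637), 10 classes at 45% use and 5 of them raised by 4 points gave 3.97 points unadjusted, 3.97 with a baseline count and 2.00 with a same-period count. The formula gives 4 × (1 − 5/10) = 2.0.

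**4. Leaving out only the analysed class.** This restores the estimate if no other class responds or if use of the classes is independent. With correlated use and all targeted classes responding, the mixed-drug scenarios still fell to between 2.02 and 3.35 points.

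**5. Nominal meaning for power.** Putting shrunken effects into the step 1 formula gives 0.72 at 3.4 points, 0.46 at 2.5 and 0.20 at 1.5. These are rough, because the formula is not the planned longitudinal model.

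**The case against.** The strongest reply is that a baseline count was probably intended. The stated purpose is to remove pre-existing differences between the groups, and Table 2 reports Charlson, a companion covariate, as a baseline characteristic. The regression equation is in Figure 2, which was not available for this review and might show how covariates are indexed. A journal article may also leave a covariate's window to the full plan. This stands to the extent that a reader might infer that the plan does adjust away part of the uptake effect, and the documents do not support that. They do not say that the count is updated after the start.

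Other limits also stand:
- The statement that the "unit of observation is the patient-quarter" belongs to the adherence series. Uptake uses one-year windows, and its analysis section names no regression, so it is the general covariate statement that reaches uptake.
- It would be too strong to say that adjustment removes the spending effect. Better adherence among existing users, shifts between tiers and the move of co-payment from patient to payer can all change spending without changing the count.
- A similar problem with Charlson would need coding to change differently in the two groups. Nothing in the article suggests this, and it was not simulated.
- The sizes rest on assumed inputs, and the single-class case is mild.

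The reply does not dispose of the point. The article commits to a covariate that its own hypotheses say will rise. Elsewhere it labels baseline or pre-intervention values as such (Table 2, Statistical power), but not here. With 15 rows in Table 1 and hypotheses 1 and 3 expecting several therapies to rise together, the single-class case is not the one the trial anticipates.

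**Conclusion.** The concern holds in conditional form. The medication count is not tied to the pre-intervention period and does not exclude the class analysed. If it is taken from post-intervention windows, the uptake effect is biased towards zero. On the assumptions above (linear model, similar classes, equal responses), the loss from a 3.8-point effect runs from roughly 10% to nearly all, with one third to two thirds when many but not all counted classes respond. The direction follows from the structure as long as the intervention raises the count; the size depends on inputs that the article does not give. Pharmaceutical spending is partly exposed, and MPR among users less directly. The power statement is sound. Because a literal same-period reading would give a worse answer on a primary outcome, the wording should be settled before the post-period data are analysed.

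**What to change.** State that the number of medications is measured once per patient from claims before 1 July 2006, or at cohort entry for those who join later, with the same rule in the control group, and is held constant over all periods. Give the look-back length; the 12 months already used to identify patients would serve. Treat Charlson in the same way as a precaution. Age and member status need not be frozen.

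Fixing the count in time is the essential step. Leaving out the analysed class is not enough on its own when several classes respond.

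The cost is one sentence. For patients in the initial groups, claims from the 30 months before the intervention are already part of the design. The downside is small: new employees, who are enrolled automatically on their first eligible claim, may have little or no look-back, so their count will be less precise. If a baseline count was always intended, nothing else changes.

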##### Statistical power

The intervention can increase appropriate medication use in two ways: by increasing use in those currently not on the medications of interest (*i.e*., increasing uptake), and by increasing the adherence of patients who are taking the medications. Based upon our original estimated sample sizes of 2,131 in the intervention group and 4,000 in the control group, and an average initial uptake rate of 50% (based upon statins and ACE/ARBs), we will have 80% power to detect an effect of 3.8% change in medication utilization at a p = 0.05 significance level. In turn, based upon average pre-intervention medication adherence rates of 65% (based on statins and ACE/ARBs), we will have 80% power to detect an effect of 3.5% change in MPR (*i.e*., adherence) at the p = 0.05 significance level.

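### The stated 80% power for a 3.5% change in MPR appears to count every patient, although adherence is tested only among users of each drug class, about half the cohort; the figure is not supported as derived

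*Protocol article*

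**What the plan says.** The Statistical power section of the protocol article starts from "original estimated sample sizes of 2,131 in the intervention group and 4,000 in the control group". These are counts of patients with diabetes, not of users of any one drug class. For uptake it assumes "an average initial uptake rate of 50% (based upon statins and ACE/ARBs") and concludes "we will have 80% power to detect an effect of 3.8% change in medication utilization". It then turns to adherence, assumes "average pre-intervention medication adherence rates of 65% (based on statins and ACE/ARBs"), and concludes "we will have 80% power to detect an effect of 3.5% change in MPR". It gives no second pair of sample sizes and no SD for MPR.

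Two places restrict adherence to users. Hypothesis 1 says that those with reduced co-payments will "improve adherence to these therapies (conditional upon their use"). The power section describes the second route to better medication use as "by increasing the adherence of patients who are taking the medications".

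Under Primary outcomes, MPR is the share of days in a quarter covered by a refill, calculated separately for each class. It is therefore a continuous measure from 0 to 100%. The Study design and Medication adherence sections analyse it as repeated patient-quarters over 30 months before and 30 months after the change, by segmented regression.

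**The concern.** The adherence figure seems to combine a mean that comes from users with a sample size that comes from everyone. If half of each group does not take the class in question, that half contributes no MPR to an analysis conditional on use. For any given SD, halving both groups multiplies the detectable change by √2 = 1.41.

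Adherence is one of the two primary outcomes. Readers of a null adherence result may take the 3.5-point figure as the size of effect that the study was able to detect. The figure should therefore rest on the patients who are actually analysed.

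**Working it through.** **Inputs.** From the Statistical power section: 2,131 and 4,000 patients, uptake 50%, mean MPR 65%, detectable changes 3.8 and 3.5 points, power 80%, alpha 0.05. Sidedness is not stated; two-sided reproduces the figures, and one-sided would give 87% for MPR. From Table 2: enrolled 2,507 and 8,637; statin use 44.7% and 44.5%; ACE/ARB use 43.4% and 48.7%. Throughout, 3.5% is read as percentage points, because a relative 3.5% would give only 43% power on all patients.

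**Step 1: reproduce the stated figures.** Two proportions, no continuity correction:

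power = Φ[(d − 1.96·SE0)/SE1], where SE0 = √(p̄(1−p̄)(1/n1+1/n2)), SE1 = √(p1(1−p1)/n1 + p0(1−p0)/n2), and p̄ is the pooled proportion.

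- Uptake, 50% vs 53.8%, all patients: power 81.0%; detectable change at 80% power 3.75 points (stated 3.8).
- MPR, 65% vs 68.5%, all patients: p̄ = 0.6622, SE0 = 0.01268, SE1 = 0.01257. Power = Φ[(0.035 − 0.02486)/0.01257] = 79.0%; detectable change 3.54 points (stated 3.5).

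One formula with one pair of sizes gives both published figures. It therefore appears that all patients were counted and that MPR was handled as a yes/no variable.

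**Step 2: whose mean is 65%?** With 50% users and non-users scored 0, the cohort mean could not exceed 0.50 × 100% = 50%. A mean of 65% can therefore only be a users' mean.

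**Step 3: same method, users only.**

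| Patients counted | Intervention / control | Power for 3.5 points | Detectable change |
|---|---|---|---|
| All planned | 2,131 / 4,000 | 79% | 3.54 points |
| Planned users, 50% | about 1,066 / 2,000 | 50% | 5.0 points |
| Enrolled statin users | 2,507 × 0.447 ≈ 1,121 / 8,637 × 0.445 ≈ 3,843 | 59% | 4.5 points |
| Enrolled ACE/ARB users | 2,507 × 0.434 ≈ 1,088 / 8,637 × 0.487 ≈ 4,206 | 58% | 4.5 points |

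**Step 4: MPR as a continuous measure.** The yes/no SD is √(0.65 × 0.35) = 0.477. That is the largest SD a 0–1 measure with mean 0.65 can have; it occurs only if every patient scores 0 or 1. The document gives no SD, so the values below are assumptions. Power = Φ[0.035/(SD·√(1/n1+1/n2)) − 1.96].

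| Assumed SD | Planned users | Enrolled users (statins; ACE/ARB agree to the nearest point) |
|---|---|---|
| 0.30 | 87% | 93% |
| 0.33 | 80% | 88% |
| 0.35 | 75% | 84% |
| 0.40 | 64% | 73% |
| 0.477 (maximum) | 49% | 58% |

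The SD at which power for 3.5 points equals 80% is 0.035/(2.80·√(1/n1+1/n2)). This is about 0.33 at planned users (√ term 0.0379) and about 0.37 at enrolled users (√ term 0.0339 to 0.0340).

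**The case against.** The strongest reply is that 3.5 points may be about right. Planned users with an SD of 0.33 give 2.80 × 0.33 × 0.0379 = 3.5 points, exactly the stated figure, and the article does not print its formula. A users-only calculation with a continuous SD therefore cannot be excluded. This stands as far as it goes. However, the paragraph gives only one pair of sizes, moves straight from uptake to adherence, and mentions no SD, while one formula on all patients explains both figures. If a users-only calculation was done, the text does not show it.

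A reader might infer that the promised power is not delivered, or that it is 50% rather than 80%. The document does not support either statement. The 50% and the 5.0 points require the maximum variance, whereas the article defines MPR as a continuous share of covered days. Overcounting patients and overstating the variance work in opposite directions, and they cancel at an SD of about 0.33. The enrolled groups are also larger than those in the calculation.

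The planned analysis also uses repeated quarters and a before-after contrast. These can move power either way, so a single-timepoint comparison settles the matter in neither direction. Finally, the groups were identified from claims rather than recruited to a power target, so nothing in conduct depends on the sentence. That lowers the severity but does not make the derivation sound.

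Nor is this a request for detail that an article may leave to a fuller document. The stated figure does not fit the hypothesis and the uptake rate stated alongside it.

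**Conclusion.** The concern holds in limited form and is of moderate severity. The statement of 80% power for 3.5 points is not supported by its apparent derivation, which counts about twice as many patients as the adherence hypothesis can use. On that same method, users only give about 50% power and 5.0 points at planned sizes, and 58% to 59% and 4.5 points at enrolled sizes.

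These are results of the method as apparently applied, not estimates of true power. True power among users could lie on either side of 80%: above it if the SD of MPR is below about 0.33 (planned) or 0.37 (enrolled), and below it otherwise. This ignores the repeated measures.

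The conclusion rests on a two-sided test, on 3.5% meaning percentage points, on baseline use rates approximating the share analysed, and on the inference from Step 1 about how the figure was obtained.

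**What to change.** Recompute the detectable change in MPR separately for statins and ACE/ARBs, on the number of users (enrolled sizes with the Table 2 use rates). Treat MPR as continuous, state its SD and the within-patient correlation across quarters, and base the calculation on the planned before-after comparison between groups. The 30 months of pre-intervention claims should allow the SD and the correlation to be estimated; if they remain uncertain, show a range. Replace the 3.5% claim with the result.

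The 5.0 or 4.5 points above should not be printed in its place, because they keep a yes/no variance for a continuous measure.

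The cost is one recalculation and a change of text. Enrolment, data collection and analysis are unaffected. The restated figure may be less favourable than 3.5 points.

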### Statistical analyses

#### Medication utilization (or uptake)

We classify an individual as utilizing therapy if any of their dispensed medications include a drug within the drug class of interest, either alone or in combination with another drug during each of the two one year windows in the pre-period and two one-year windows in the post-period. For analysis purposes, ACE-Inhibitors and ARBs are considered one drug class.

